### Sample size calculation

In Dutch nursing homes the prevalence of pressure ulcers is about 30% for all grades and about 12% for grade 2 to 4 [4]. Few studies have investigated incidence rates for Dutch nursing homes: one study found an incidence rate of 25% in the first four weeks after admission [10]. The first studies [1,2] on the Australian Medical Sheepskin found incidence rates of 30% in the control group and 9.6% for the intervention group.

For this study we will consider the Australian Medical Sheepskin to be effective and clinically significant if the incidence rate in the first month after admission is at least (in absolute terms) 10 percentage points lower in the experimental group than in the control group. This means that with an expected maximum incidence rate of 18% in the experimental group and about 28% in the control group, 750 patients (2 × 375) are needed to find such differences with a power of at least 80% and a two-sided alpha of 0.05.

Halfens *et al.*[4] state that 68% of the pressure ulcers in nursing homes originate during the nursing home stay; accordingly, with a prevalence of 30%, this means that approximately 10% of the patients are admitted with an already existing pressure ulcer, and will therefore not fulfill our inclusion criteria. Furthermore, it is expected that about 10% of the patients will refuse to participate and that about 5% will drop-out from the study for other reasons (e.g. not being able to discuss matters and give informed consent). Allowing for drop-out and for the fact that not all patients are pressure ulcer free when admitted to the nursing home, 1000 patients (2 × 500) will be recruited. Based on the admission data of previous years, it is assumed that about 1,350 patients will be admitted in the planned 18 months of patient inclusion. The expected patient inclusion flow is shown in Figure 1.

**Figure 1 F1:**
[figure not shown]
Flow chart expected patient inclusion.

### Patient allocation/randomisation sequence/blinding

All newly admitted patients will be checked by the nurse in charge at admission to ascertain whether they fit the inclusion criteria. If so, they will be given research information in written format and verbally by the same nurse at admission. On the next day they will be asked for informed consent (by the same nurse) and if they agree, the nurse will immediately call the central research office to find out to which group the patient has been randomized. Thus, the therapy according to randomization status will start immediately and within less than 48 hours after admission.

To ensure concealment of allocation, a randomization scheme was created in SPSS by assigning the intervention to a random sample of circa 50% in a list of 1,500 numbers and assigning the control group to the rest. This allocation of the group (sheepskin, usual care) was then blinded on a paper list numbered 1 through 1,500 by a secretary not further involved in the project. Each time a patient is admitted, the principal investigator located at the central research office is called. The above list with numbers and blinded allocation is held at this office. This central research office registers each patient identity for every consecutive number and discloses the group allocation to the nurse and patient.

Only the patient allocation itself is blinded to all parties involved, because it is impossible to blind health professionals or patients to whether someone is in the sheepskin group or not.

### Intervention

The experimental condition consists of the application of the Australian Medical Sheepskin as an overlay on top of the standard/usual mattress in the area of the buttocks and in the (wheel)chair, combined with all care as usual. An extra Australian Medical Sheepskin at the bottom of the bed is also permitted. The intervention will start no later than 48 hours after admission. The Australian Medical Sheepskin will be applied during the first 30 days after admission (and prolonged if the patients wish so, but without gathering research data). The period of 30 days is chosen because most pressure ulcers develop in the first weeks after admission [6,10,36,37]. The sheepskins will be changed at least every two days.

Besides the use of the Australian Medical Sheepskin, all other usual pressure ulcer preventative interventions such as mobilization and repositioning may be added as co-interventions, in so far as they are normally used in the participating nursing homes. All other nursing care can be continued as usual (including incontinence materials).

The control group will receive usual care, including all the pressure relieving interventions and other preventive actions, normally taken in the participating nursing homes. The application, in any way, of the Australian Medical Sheepskin is forbidden in this group.

### Outcomes

A distinction can be made between variables relating to the effectiveness (incidence, prevalence of pressure ulcers) and variables relating to costs (purchase and washing of the sheepskins on the one hand, and investment of time and materials cost for pressure ulcer treatment on the other). Both of these are necessary to compute cost-effectiveness.

The primary outcomes for this study are:

- the incidence of sacral pressure ulcers in the first 30 days after admissions,

- the costs of appliance of the sheepskin, and

- the costs related to treatment of the pressure ulcers that have developed.

Secondary outcomes are the presence of pressure ulcers on other places, quality of life, comfort of the sheepskin as experienced by the patients and ease of use of the sheepskin as experienced by the care personnel.

Influencing factors that will be measured are patient characteristics, the application of other pressure relieving interventions and materials and the use of incontinence materials.

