**Methods/Design:**

In a multi-centre randomised controlled trial 750 patients admitted for a primarily somatic reason to one of the five participating nursing homes, and not having pressure ulcers on the sacrum at admission, will be randomized to either usual care only or usual care plus the use of the Australian Medical Sheepskin as an overlay on the mattress.

Outcome measures are: incidence of sacral pressure ulcers in the first month after admission; sacrum pressure ulcer free days; costs; patient comfort; and ease of use. The skin of all the patients will be observed once a day from admission on for 30 days. Patient characteristics and pressure risk scores are assessed at admission and at day 30 after it.

Additional to the empirical phase, systematic reviews will be performed in order to obtain data for economic weighting and modelling.

The protocol is registered in the Controlled Trial Register as ISRCTN17553857.

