### Participants

The study population will concern patients newly admitted for a primarily somatic condition to one of the five participating nursing homes. Only patients who are free of sacral pressure ulcers on admission will be included. Further inclusion criteria are: adult; not having darkly pigmented skin (because of difficulty in diagnosing grade 1 pressure ulcer); having an expected stay of more than one week; and consenting to the research.

For practical reasons and because 74% of nursing home patients in the Netherlands are at risk for pressure ulcer development [4], we have chosen to involve all patients, and not only patients at risk.

The patients will be recruited from 5 different Dutch nursing home care groups (Amstelring, Florence, Frankeland, Sutfene, Swinhove) involving seven different geographical locations and 18 wards. The selection of the nursing homes was made on the basis of the customer list of the laundry company that we contacted, and which is able to do the washing and drying of the sheepskin, according to the Australian Standard [35].

Inclusion of patients started on May 1^st ^2007 and will proceed until the targeted number of patients is reached, for a maximum of 1.5 years. It is expected that enough patients will be admitted during this period to reach the necessary number as was calculated by power-analysis.

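### Eligibility and the outcome window start at admission but randomisation follows the next day, so sacral ulcers arising in the roughly one-day gap count as incident events that no allocation could affect

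*Protocol article*

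**What the plan says.** Four statements in the protocol article fix the timing.

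- **Eligibility.** Under Participants: "Only patients who are free of sacral pressure ulcers on admission will be included". The section on allocation, randomisation and blinding places the check at the same moment: "All newly admitted patients will be checked by the nurse in charge at admission to ascertain whether they fit the inclusion criteria".
- **Consent and randomisation.** The same section continues: "On the next day they will be asked for informed consent (by the same nurse) and if they agree, the nurse will immediately call". That call goes to the central office, which discloses the group.
- **Start of treatment.** Also there: "the therapy according to randomization status will start immediately and within less than 48 hours after admission". The Intervention section repeats the limit: "The intervention will start no later than 48 hours after admission".
- **Outcome window.** The first primary outcome under Outcomes is "the incidence of sacral pressure ulcers in the first 30 days after admissions". The abstract has the observations on the same clock: "The skin of all the patients will be observed once a day from admission on for 30 days".

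The article does not say that the sacrum is looked at again before the call, that counting begins at randomisation, or that ulcers first seen before the call are left out.

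**The concern.** A patient can pass the admission check, develop a sacral ulcer by the next day, consent, be randomised, and be counted as an incident case. The sheepskin had no opportunity to prevent that ulcer, because the arm had not yet been drawn. The patient already has the outcome on entering a prevention comparison.

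Two features of the plan make this more than tidiness. First, the Sample size calculation section calls the sheepskin effective only if incidence is at least 10 percentage points lower in absolute terms, and events common to both arms shrink exactly that quantity. Second, the Intervention section justifies the 30-day period by saying that most ulcers develop in the first weeks after admission, so the opening days cannot be assumed to be event-free.

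Ulcer-free days, the Kaplan-Meier analysis of onset and the treatment-cost outcome draw on the same ulcers, and the Data-analysis section names no other time origin for them.

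**Working it through.** **Inputs from the article.** Control incidence 28%, experimental 18%, 375 per arm, two-sided alpha 0.05, power of at least 80% (Sample size calculation); two-sided chi-square test (Data-analysis); 30-day window from admission (Outcomes).

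**Assumed, because the article gives no figure.** The share s of control-arm events that occur before allocation.

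**Step 1: the plan's own figure.** With the usual normal approximation for two proportions,

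power = Φ{[d − 1.96·√(2·p̄(1−p̄)/n)] / √([p_c(1−p_c) + p_t(1−p_t)]/n)}.

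For d = 0.10, p̄ = 0.23 and n = 375, the two standard errors are 0.0307 and 0.0305, and power is 90.4%. For 80% power the formula needs 277 per arm; for 90% it needs 371. So 2 × 375 does meet the stated minimum of 80%, with room to spare.

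**Step 2: length of the gap.** The 48 hours run from admission and cap the start of treatment. Consent comes the next day, the call follows at once, and treatment follows the call at once. The time before allocation is therefore about one day, with two days as the outer limit.

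**Step 3: share of events in the gap at constant hazard.** A 30-day risk of 28% means a 30-day event-free probability of 0.72.

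- One day: 1 − 0.72^(1/30) = 0.0109, i.e. 1.1% of patients; s = 0.0109/0.28 = 3.9%; 750 × 0.0109 ≈ 8 ulcers.
- Two days: 1 − 0.72^(2/30) = 0.0217, i.e. 2.2% of patients; s = 0.0217/0.28 = 7.7%; 750 × 0.0217 ≈ 16 ulcers.

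**Step 4: dilution.** Suppose the planned risk ratio 18/28 applies only to ulcers arising after allocation. Then p_c = 0.28 and p_t = 0.28·s + 0.28·(1 − s)·(18/28) = 0.28·s + 0.18·(1 − s), so the difference is 0.10·(1 − s).

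| Share s before allocation | Experimental incidence | Difference (points) | Power, 375 per arm |
|---|---|---|---|
| 0 | 18.0% | 10.0 | 90% |
| 3.9% (one day, constant hazard) | 18.4% | 9.6 | 88% |
| 7.7% (two days, constant hazard) | 18.8% | 9.2 | 85% |
| 13% (hypothetical) | 19.3% | 8.7 | 80% |
| 15% (hypothetical) | 19.5% | 8.5 | 78% |
| 20% (hypothetical) | 20.0% | 8.0 | 73% |

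Power crosses 80% at s of about 13%. For a one-day gap, s = 15% is 15/3.9 ≈ 3.9 times the constant-hazard share, and s = 20% is 20/3.9 ≈ 5.1 times.

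**Step 5: with an ulcer-free check at the call**, still 375 randomised per arm and observation ending at day 30 after admission. Control risk becomes 0.28(1 − s)/(1 − 0.28s), and 18/28 applies to all of it. One day: 27.2% versus 17.5%, power 89%. Two days: 26.4% versus 17.0%, power 88%.

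**The case against.** The strongest reply is that the admission clock is deliberate and consistent. Research question 1 asks about the first month after admission, and the sample size section states its 18% and 28% on that clock, so those rates nominally include early events. This stands: the calculation shows no error in the sample size, and Step 4 is conditional on reading 28% versus 18% as the effect on ulcers arising after allocation. What it does not answer is that part of the window lies before allocation, whatever rates are assumed.

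A reader might go further than the document allows in three ways.

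- *That treatment may start up to 48 hours after randomisation.* It may not: the limit runs from admission. Any short interval between the call and the sheepskin is after randomisation and belongs in the intention-to-treat comparison.
- *That the trial is biased.* Ulcers arising before the arm is drawn cannot depend on the arm. They are balanced in expectation, type I error is unaffected, and the dilution is conservative.
- *That the trial misses its 80% power.* This needs s above about 13%. The statement that most ulcers arise in the first weeks does not establish such concentration in the first day.

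It is also fair that this is a condensed article and that the admission and daily forms are not shown. They might deal with an ulcer seen on the consent day. The point therefore rests on what the article itself states about eligibility and the outcome window.

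**Conclusion.** The point holds at modest size. Following the article as written, sacral ulcers that arise between the admission check and the randomisation call are counted as incident events in an arm drawn afterwards.

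The most plausible case, one day at constant hazard, costs about 0.4 of a percentage point and about 2 to 3 points of power (90.4% to 87.8%). The outer case of two days costs about 0.8 of a point and brings power to 85%. Both stay above the stated 80%. These figures assume that the planned risk ratio acts only on ulcers arising after allocation, and they make no allowance for drop-out or for clustering by ward. The early hazard is unknown; if it is above average the loss is larger, but the article offers nothing to quantify it.

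The reason to act is that the success criterion is an absolute 10-point difference, which these events erode directly, and that removing them is cheap.

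**What to change.** 1. At the randomisation call, have the nurse confirm, and the central office record, that the sacrum is ulcer-free, using the daily observation already made. Do not randomise a patient with a sacral ulcer at that check.
2. Define the primary outcome, ulcer-free days and time to onset by the first sacral ulcer after randomisation. Keep the existing end of observation at day 30 after admission. Running to day 30 from randomisation would need observations beyond those planned.
3. State that the 10-point criterion refers to this outcome.
4. Report ulcers found between admission and randomisation separately.
5. Inclusion began in May 2007. For patients already enrolled, exclude from the primary analysis only those whose sacral ulcer is documented on a day before the randomisation day. The article describes one observation a day, and nurses know the allocation after the call. Same-day records of unclear order should therefore stay in the primary analysis and be excluded in a sensitivity analysis.

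**Cost.** One extra item on a call that already takes place, revised outcome wording, and the loss before randomisation of a small number of patients: about 1% at constant hazard over one day, or roughly 8 per 750. No follow-up is added. The window after randomisation becomes about a day shorter than 30 days, equally in both arms.

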### Instruments

These outcomes, as well as influencing factors, will be measured by appropriate instruments, as far as possible we will use already existing and validated instruments. The EPUAP grading system is used to assess the presence and severity of pressure ulcers [38].

To this end a 'daily observation checklist' has been developed. Nurses use this checklist during the first 30 days after admission to report the presence/absence of sacral pressure ulcers, as well as the ulcer grade; the presence/absence of pressure ulcers on other locations and whether a sheepskin, repositioning, other support surfaces and incontinence material are applied.

When nurses feel uncertain about their observations they are instructed to call another specialized nurse, experienced in observing pressure ulcers.

Furthermore, a photographic series of the various pressure ulcer grades is available on each ward, as well as special glasses that can be used in order to differentiate better between blanchable and non-blanchable erythema. Finally, all nursing homes are offered a lesson in pressure ulcer observation.

The daily skin observations by nurses during routine care will be checked weekly by an experienced nurse observator from the nursing home itself and bimonthly by the principal investigator from the central research office.

Influencing patient factors that will be measured are age, gender, principal medical diagnosis category, surgery in the last month, presence of pressure ulcers at admission on other places than the sacrum, incontinence status, nutritional status (including body mass index), activity of daily living level (Barthel-index) and pressure ulcer risk score (Braden-scale). These are measured twice: at admission and at day 30 after it.

Furthermore the patients in the sheepskin group are asked at the end of the research period to rate the (dis)comfort of the sheepskin. For this purpose, a self-developed 7-item questionnaire with a 5-point rating answer structure was developed.

Data about costs that will be gathered are the costs of buying sheepskins, costs of washing sheepskins, costs of treatment of pressure ulcers (medication, wound care materials, diagnostics, kind of specialized consultants and time involved, and extra time for nurses/carers with regard to pressure ulcer treatment).

For this purpose, invoices from the firms in question will be used, or the best approximations as far as these are available in Dutch (governmental) sites/organizations.

In summary, in order to register the above-mentioned data, the following five forms were created: admission form, daily observation form, end of research period form, sheepskin comfort questionnaire and the pressure ulcer therapy cost form (these forms in Dutch can be obtained on request from the first author).

The initial assessment at admission is completed for all patients that fulfill the inclusion criteria, in order to conduct a post hoc check as to whether there was selective attrition in patients not willing to participate.

Ease of use of the sheepskin for carers will be measured by group interviews to be held on three occasions during the research period.

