## Discussion

This study is innovative because it is the first to assess the cost-effectiveness of the Australian Medical Sheepskin in nursing home patients and also because current opinions and guidelines [13,41-44] oppose the use of sheepskins. However, these are based on old forms of sheepskins, not comparable to the genuine Australian Medical Sheepskin.

A difficult point in this research is that the usual care can not be standardized. Although nurses and nursing homes may have pressure ulcer protocols and say that they are following these, there is a chance that the usual care differs from nursing home to nursing home, or even from nursing ward to nursing ward, and that individual nurses may deviate from the protocol. Moreover, it is known that different mattresses are in use in and between nursing homes. Since standardization is in no way possible, a registration of mattresses and devices applied will be conducted.

With regard to possible contamination between experimental and control group, the following measures will be taken: clear instruction to all nursing and care personnel and patients, a limited stock of sheepskin on the ward, daily inspection of the skin by the research team in both groups, and a concise control and observation to ascertain whether the patients are still being nursed in the condition they were randomized to. Moreover it is not very likely that patients from both groups will be nursed on the same room during the same period (1.2 admissions per bed); therefore it is improbable that patients from the control group will ask for a sheepskin.

Finally, in the information sessions with nurses, it will be stressed that the Australian Medical Sheepskin is NOT a replacement for the normal pressure relieving interventions such as repositioning and other methods.

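### All-grade sacral ulcers are judged by ward nurses who know the arm, with no masked check described and no grade 2-4 analysis named; differential calling of grade 1 could materially inflate or mask the effect

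*Protocol article*

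**What the plan says.** Outcomes in the protocol article lists the 30-day incidence of sacral ulcers first among the primary outcomes and sets no grade threshold. Grade 1 evidently counts: Participants excludes darkly pigmented skin because grade 1 is hard to diagnose there, and Instruments supplies glasses for telling blanchable from non-blanchable redness.

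Under Instruments, ward nurses fill in a daily checklist. It records sacral ulcer, its grade and whether a sheepskin is in use. On masking, the section on allocation and blinding says that "it is impossible to blind health professionals or patients to whether someone is in the sheepskin group or not".

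Instruments also lists safeguards: a specialised nurse to call when in doubt, photographs and glasses on the wards, an offered lesson, and two layers of checking. "The daily skin observations by nurses during routine care will be checked weekly by an experienced nurse observator from the nursing home itself", and the principal investigator checks bimonthly. None of these is described as masked. The principal investigator's office also holds the randomisation list and discloses allocations.

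Data-analysis names a chi-square test for incidence, a t-test for ulcer-free days and Kaplan-Meier curves. It names no analysis by grade.

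On the mix of grades, Sample size calculation says that "the prevalence of pressure ulcers is about 30% for all grades and about 12% for grade 2 to 4".

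The Discussion lists among its measures against contamination "daily inspection of the skin by the research team in both groups".

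**The concern.** An unmasked trial can still have a robust outcome if the outcome is hard to misjudge. Grade 1 is the grade that the article itself treats as difficult, and the person judging it knows whether the patient lies on a sheepskin. If nurses call redness more readily in one arm, the chi-square test cannot separate that from a sheepskin effect. The ulcer-free-days and time-to-onset analyses use the same daily records, so they inherit the same problem.

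Training, photographs and a second opinion may make calls more accurate on average, but they do not stop calls from depending on the arm.

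The Discussion makes this harder to see. A reader of that section alone would credit the trial with daily inspection by researchers, whereas Instruments gives the daily observation to ward nurses and gives the research office only a bimonthly check.

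**Working it through.** **Inputs.** Sample size calculation assumes "an expected maximum incidence rate of 18% in the experimental group and about 28% in the control group". It plans 375 per arm, sets alpha at 0.05 (two-sided) and takes 80% as the minimum power. The prevalences are 30% and 12%, from the same section. The article gives no size for differential calling; 20% is my illustration.

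**Method.** Two-proportion test with n = 375 per arm, normal approximation. With d = p1 − p2 and p̄ the mean of p1 and p2, se0 = √(2p̄(1−p̄)/n) and se1 = √((p1(1−p1) + p2(1−p2))/n). The chance of a significant result favouring sheepskin is Φ((d − 1.96·se0)/se1).

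**1. The plan's own figure.** For 28% v 18%, se0 = 0.03073 and se1 = 0.03052, so power = Φ((0.10 − 0.0602)/0.0305) = 90.4%. The stated power of at least 80% is met; 277 per arm would give 80% and 371 would give 90%.

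**2. Grade 1 share.** (30 − 12)/30 = 60%. At 28% incidence, that is 16.8 points of grade 1 and 11.2 points of grade 2-4. The prevalences are not restricted to the sacrum or to new ulcers, so the 60% is an assumption, varied from 40% to 70%.

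**3. No true effect, grade 1 called 20% more readily in controls.** The control rate becomes 28% × (1 + share × 0.20), and the sheepskin rate stays at 28%.

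| Grade 1 share | Control rate | False benefit | Chance of significant benefit |
|---|---|---|---|
| 40% | 30.2% | 2.2 points | 10% |
| 60% | 31.4% | 3.4 points | 17% |
| 70% | 31.9% | 3.9 points | 22% |

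The nominal chance in that direction is 2.5%. At a 60% share, 10% over-calling gives 1.7 points and 7%; 30% gives 5.0 points and 32%. The mirror case, 20% under-calling in the sheepskin arm, gives 3.4 points and 18%.

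**4. Planned effect present, grade 1 under-called by 20% in controls.** The control rate becomes 28% × (1 − 0.6 × 0.20) = 24.6%. The difference from 18% is 6.6 points and power falls from 90% to 60% (73% at a 40% share, 53% at a 70% share).

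**5. What it takes to manufacture a result.** In the under-calling model, an observed difference of about 6.2 points is significant: 6.2/16.8 = 37% differential calling. The full 10-point target needs 10/16.8 = 60%.

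**6. Grade 2-4 alone.** With a 40% share and the same relative effect, 0.4 × 28% = 11.2% v 0.4 × 18% = 7.2%. Power at 375 per arm is 47%, and 80% would need 819 per arm. If grade 2-4 makes up 30% to 60% of ulcers, power is 37% to 66%.

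**7. Who inspects daily.** Instruments says ward nurses, checked weekly by a nurse of the same home and bimonthly by the principal investigator. The Discussion says the research team, daily. Both cannot describe the same procedure.

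**The case against.** The strongest reply has four parts.

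- **The analysis may exist elsewhere.** Grade is recorded daily, primary outcomes are first described, and a condensed article may leave an analysis by grade to a fuller plan. This stands. A reader might infer that grade 2-4 ulcers will not be analysed; the article supports only that no such analysis is named here.
- **The case rule is unknown.** A reader might infer that one unconfirmed record makes a case, so that false positives pile up over 30 checks. The article is silent on confirmation in either direction. The size of such an effect also depends on an unsourced daily error rate: with errors independent across days and added to 28% v 18%, 0.5% per day cuts power to 70%, but 0.1% leaves 87% and 0.2% leaves 82%. I do not rely on it.
- **Modest bias does not by itself create the effect.** This stands too. At 20% over-calling a false significant benefit is still missed about 83% of the time, and step 5 shows that much larger differences are needed to reach significance on average.
- **Safeguards exist.** The second nurse, photographs, glasses, lesson and checks may well limit miscalling. They do not remove its dependence on the arm, because none is described as masked.

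That sheepskin use cannot be masked is also true. It is a reason to report a less subjective outcome alongside the primary, not a reason to do without one.

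**Conclusion.** The concern holds in a limited form. The primary outcome includes grade 1, its assessors know the arm, and no masked check is described. Differential calling of grade 1 could therefore materially inflate the chance of a false benefit (2.5% to about 17% at 20% over-calling in controls) or hide a real one (power 90% to about 60% at 20% under-calling in controls). These sizes rest on two assumptions: the 60% grade 1 share and the 20% calling difference. Nothing in the article shows that such a difference will occur or how large it would be, so the result should not be read as predicted to be biased.

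The mismatch between the Discussion and Instruments rests on no assumption and needs correcting in any case.

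**What to change.** 1. Before any analysis by arm, prespecify sacral grade 2-4 incidence by arm, with the difference and 95% CI, as a supportive analysis. With about 47% power it should be neither a primary endpoint nor a condition for claiming benefit. State that an all-grade benefit confined to grade 1 will be interpreted with caution.
2. Leave the primary case definition unchanged, because inclusion began in May 2007 and the trial is open. As a sensitivity analysis only, count grade 1 when it is recorded on two consecutive daily checks or confirmed at the existing weekly check.
3. Reconcile the Discussion with Instruments on who inspects the skin daily.

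The cost is a little wording and extra analysis: grade is already recorded daily and the weekly check already exists. The downside is a supportive result with low power, which may be inconclusive by itself. Neither analysis masks the assessor; they show how far the conclusion depends on grade 1.

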With regard to treatment adherence, patients from the intervention group are asked only to keep the sheepskin in their bed for 30 days. No other action is required from patients other than actions that are also asked in the control group. However it remains possible that some patients after a few days will refuse the sheepskin (e.g. because of itching, not feeling comfortable, too hot, or other reason): in these cases the use of the Australian Medical Sheepskin will be stopped without persuading patients to continue, but they will be asked if the daily skin observations can be continued. Records will be kept of patients that have discontinued the use of the Australian Medical Sheepskin (including reasons to stop), and they will be analyzed in the group they were randomized, according to intention to treat analysis principles.

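### Sheepskin comfort is rated once, at the close of the research period, so patients who give it up early are rated late or perhaps not at all, which risks a flattering score

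*Protocol article*

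**What the plan says.** - **Status.** The Outcomes section lists comfort as a secondary outcome: "Secondary outcomes are the presence of pressure ulcers on other places, quality of life, comfort of the sheepskin as experienced by the patients". Research question 6 asks how patients and staff rate it.
- **Instrument and timing.** Under Instruments, "a self-developed 7-item questionnaire with a 5-point rating answer structure was developed", and "the patients in the sheepskin group are asked at the end of the research period to rate the (dis)comfort of the sheepskin". No other occasion for this rating is described.
- **Period of use.** Under Intervention, "The Australian Medical Sheepskin will be applied during the first 30 days after admission".
- **Early refusal.** The Discussion's paragraph on treatment adherence allows that "some patients after a few days will refuse the sheepskin (e.g. because of itching, not feeling comfortable, too hot, or other reason". Of these patients it says "they will be asked if the daily skin observations can be continued". It adds that discontinuations and their reasons will be recorded and that these patients will be analysed in their randomised group. It does not mention a comfort rating at the time of stopping.
- **Length of stay.** Under Participants, one criterion is "having an expected stay of more than one week", so a patient can be eligible and still be discharged before day 30.

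**The concern.** The timing of the rating sits badly with the protocol's own expectations. The foreseen reasons for stopping (itching, heat, discomfort) are what a comfort questionnaire is meant to measure. The patients with most to report are therefore the ones furthest from their experience of the sheepskin when the questionnaire arrives, and the ones who may have withdrawn from further contact.

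If they are not rated, missing ratings depend on the outcome itself, and the reported score leans towards patients who tolerated the sheepskin. Comfort bears on whether nursing homes can adopt the overlay, so a flattering score would mislead on a practical question the trial sets out to answer.

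**Working it through.** The protocol states no figure for comfort, so there is nothing to reproduce. The check has two parts.

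**1. What happens to each kind of patient under the schedule as written**

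| Patient | When rated | Consequence |
|---|---|---|
| Uses the sheepskin to day 30 | At the end | No problem |
| Stops early, agrees to continued skin observation | At the end, from memory | Delay. If use stops on day 4 and the rating is on day 30, the gap is 30 - 4 = 26 days. Recall error, of uncertain sign |
| Stops early, declines further participation | Not described | Possibly unrated, for a reason linked to comfort |
| Leaves before day 30 for unrelated reasons | Not described | Possibly unrated. Fewer ratings, but no necessary shift in the mean |

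Only the third row points clearly in favour of the sheepskin.

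The timing phrase is also loose. The same section uses day 30 explicitly for the repeat risk measures but words the comfort rating differently. It later applies the term research period to the span over which three staff group interviews are held, which appears to be the whole trial. The comfort rating might therefore fall on day 30 or on the patient's own last study day.

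**2. How large a bias could be, on assumed values**

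Let q be the share of sheepskin patients not rated. Then:

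excess in the reported mean = mean of raters - mean of all users = q x (mean of raters - mean of non-raters)

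Input from the protocol: 375 patients per group (Sample size calculation). Everything else is assumed: items scored 1 to 5 with higher meaning more comfortable, raters averaging 4.0, unrated stoppers averaging 2.0 or 3.0, and q from 5% to 30%.

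| q | Patients (q x 375) | Excess if stoppers average 2.0 | Excess if stoppers average 3.0 |
|---|---|---|---|
| 5% | about 19 | 0.05 x 2.0 = 0.10 | 0.05 x 1.0 = 0.05 |
| 10% | about 38 | 0.10 x 2.0 = 0.20 | 0.10 x 1.0 = 0.10 |
| 20% | 75 | 0.20 x 2.0 = 0.40 | 0.20 x 1.0 = 0.20 |
| 30% | about 113 | 0.30 x 2.0 = 0.60 | 0.30 x 1.0 = 0.30 |

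If stoppers are in fact rated, or if those unrated left for reasons unrelated to comfort, the excess is about 0. The drop-out of about 5% in the sample size section cannot stand in for q: the example given there concerns consent, and it is not a rate of stopping the sheepskin.

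**The case against.** The strongest reply is that the text does not exclude stoppers. It asks the sheepskin group as a whole, with no condition of current use, and the Discussion keeps those who stop in their randomised group. A resident who gave the sheepskin up can still be handed the questionnaire. If the timing phrase means the patient's own last study day, early discharge may already be covered. Recall by people who stopped because of discomfort has no evident reason to favour the sheepskin, and nothing in the article links discomfort with leaving the nursing home. Reasons for stopping are recorded and the daily checklist shows whether a sheepskin is applied, so discomfort-related stops can be counted. The article is also a condensed account.

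Most of this stands, and it limits the point. A reader might infer that the comfort result is simply a rating by those who tolerated the sheepskin, that it is biased by some stated multiple, or that no analysis could repair it. The document supports none of these. It does not say stoppers go unasked, it gives no stopping rate, and the recorded reasons permit a partial repair.

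The schedule itself remains. The timing of the rating is stated, not left out. Even on the last-study-day reading, a stopper who agrees to continued skin observation stays in the study, so the rating is still delayed. A recorded reason is not a score on the seven items, and it does not cover patients who simply leave.

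**Conclusion.** The point holds as a risk, not as a demonstrated bias. One late rating, set beside expected early refusal for discomfort and possible early departure, means that some patients will be rated by delayed recall or may go unrated. Bias in favour of the sheepskin arises only to the extent that stoppers go unrated. The document does not allow its size to be estimated; the range of 0 to 0.60 points on a five-point scale follows entirely from assumed values.

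Comfort is a secondary outcome rated in one arm only, and the primary comparison of sacral ulcer incidence does not depend on it. This is a minor, inexpensive improvement.

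**What to change.** - Give the existing seven-item questionnaire when sheepskin use stops, when the patient leaves, or at day 30, whichever comes first, and state this trigger in place of the present timing phrase.
- Report ratings for all patients allocated to the sheepskin, with days of use, and show stoppers and completers separately.
- State the number not rated, next to the count of discontinuations and their recorded reasons.

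**Cost.** No new form and no extra staff; only the trigger for an existing questionnaire changes. The downside is that ratings will refer to different lengths of use, which is why days of use should be reported with them.
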